### Objective and research questions

The aim of this study is to evaluate the efficacy of a newly developed guided self-help Internet-based intervention (GET.ON Mood Enhancer) compared to an online psychoeducation on depression (OPD).

We expect that observer-rated depressive symptomatology assessed by raters blind to treatment conditions will be reduced to a greater extent in the intervention group than in the control condition. Moreover, we hypothesise that GET.ON Mood Enhancer is superior in terms of self-reported depressive symptoms, wellbeing, quality of life, symptoms of anxiety and problem-solving skills compared to the OPD-control condition. Potential negative effects with regard to (1) numbers of patients with symptom deteriorations, (2) attitudes towards seeking psychological help, and (3) other adverse events will be systematically evaluated. We hypothesise that both treatment conditions will not have a negative effect on attitudes towards seeking psychological help.

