#### Assessments

Self-report and observer-rated assessments will take place at baseline, post-intervention and 12-week follow-up. See Figure 1 for a detailed overview. Self-report data will be collected using a secured online-based assessment system (AES, 256-bit encrypted), and observer-based assessments will be conducted via the telephone by trained interviewers. Observer-rated assessments will be recorded to examine inter-rater reliability. In case of disagreement, the two raters will discuss until a consensus is formed, and the agreed rating will be used for analysis. If no agreement is reached after discussion, the assessment will be rated by an experienced diagnostic-rater (gold standard), and this rating will be used for analysis.

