### Sample size calculation

We aim to include 128 participants. This sample will allow us to detect a between-group effect size (ES) of d = 0.50 with a power (1-ß) of 80% and an alpha of 0.05 (calculated using PASS 12). The most recent meta-analytic review found a mean ES of d = 0.78 for therapist-supported web-based interventions for depression [19]. However, most of the included studies used a waiting-list control comparison only, and these studies showed a considerably larger ES than those studies including a treatment-as-usual condition. Our comparison condition will include psychoeducation and full access to treatment as usual and participants are encouraged to seek further help. Thus, we expect a somewhat smaller ES of d = 0.50 at post-treatment.

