### Statistical analyses

The clinical trial will be conducted in compliance with the Declaration of Helsinki, the CONSORT guidelines, GCP and the protocol. Aiming at an intention-to-treat design [61] we will include all participants who will be randomly assigned to one of the two conditions. Additional per protocol analyses (PPA) will be conducted, including only participants’ satisfying protocol treatment (completed at least 4 of 6 modules). Mixed-model analyses of variance will be conducted to explore the effects of the treatments on all continuous outcomes. Missing data will be handled using multiple imputations (MI). MI is especially robust with respect to missing data [62]. Nevertheless, to assess systematic effects of non-ignorable missing data, pattern mixture analyses for multi-level longitudinal approaches [63] will be conducted. To determine if the treatment effect is dependent on missing data, the missing-data pattern of each participant will be first coded and then included in a three-way interaction (missing pattern × condition × change in depression severity) in the main outcome analyses. If no significant interactions between missing-data pattern and treatment outcome are found, we will conclude that no missing data bias occurred in the results. For all mixed-model analyses, Cohen’s d [64] will be calculated by standardising the differences between baseline and follow-up scores by the pooled standard deviation of the baseline scores. Response and remission rates will be compared across groups with the help of contingency tables and χ2 tests. We will also calculate the number needed-to-be-treated (NNT) with GET.ON Mood Enhancer to achieve one response and remission, respectively, compared to the control group. We will also calculate the number needed-to-harm, which indicates the number of participants treated in the experimental condition for one extra person to have a symptom deterioration. Because the differential risk of the intervention ideally needs to be set into relation with its benefits we will also calculate a benefit-risk ratio [65]. Benefit-risk ratio will be calculated by dividing the NNH to achieve one symptom deterioration through the NNT to achieve one response. If this benefit-risk ratio is greater than 1, the benefits outweigh the risks; if it is 1, the balance between benefit and risks are equal across the groups; if it is less than 1, the risks outweigh the benefits (LIT). Benefit-risk ratios will only be calculated when differences in risk for symptom deteriorations are statistically significant.

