
For other negative effects, we will use independent t-tests for continuous, χ^
*2*
^ for categorical, and logistic regression for binary outcomes. In a pre-planned subgroup analysis, we will explore negative effects of GET.ON Mood Enhancer on attitudes towards seeking psychological help in patients who do not reach the response criteria up to post-assessment (6 weeks). For all statistical analyses, significance level will be set at *P* <0.05. All analyses will be conducted using SPSS 20.

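### The one spelled-out check for non-ignorable missing data tests mean severity change, so a null result cannot clear the deterioration count or the number needed to harm

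*Protocol article*

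**What the plan says.** All of this is in the protocol article.

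- **Missing data (Statistical analyses).** The handling rule is "Missing data will be handled using multiple imputations (MI". The imputation model is not described.
- **Non-ignorable missingness (same section).** The article adds that, "to assess systematic effects of non-ignorable missing data, pattern mixture analyses for multi-level longitudinal approaches [63] will be conducted". The only form it describes is that each participant's missing-data pattern is coded and "included in a three-way interaction (missing pattern × condition × change in depression severity) in the main outcome analyses". If no such interaction is significant, the authors will conclude that missing data did not bias the results. That conclusion is not restricted to any one outcome.
- **Harm outcome.** The Objective and research questions section lists "Potential negative effects with regard to (1) numbers of patients with symptom deteriorations" first among the negative effects to be evaluated. The Negative effects section defines deterioration as a reliable change index of −1.96 on the HRSD-24. Statistical analyses builds the NNH on it, and divides the NNH by the NNT to get a benefit-risk ratio, calculated only if the arms differ significantly in deterioration.
- **How the HRSD-24 is obtained.** Under Assessments, "observer-based assessments will be conducted via the telephone by trained interviewers". Under Assessment of eligibility and randomisation, people who leave treatment are still asked for all remaining assessments, or at least the primary outcome.

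**The concern.** MI under its usual assumption treats a participant with no follow-up HRSD-24 as resembling observed participants with the same recorded data. Deterioration is an endpoint for which that is open to doubt, because getting worse may itself be a reason not to take the telephone interview. It is also a tail event, so a few unobserved cases matter: at 64 per arm (1:1 assumed), one participant moves a rate by 1/64, or 1.6 percentage points.

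The plan recognises non-ignorable missingness, but the check it describes concerns mean change in severity. A null result would then be carried over to every result, harm included. What is at stake is the reported deterioration rate, the NNH, and whether the benefit-risk ratio is calculated at all. The Discussion gives negative effects special emphasis and ties wide dissemination partly to an acceptable balance of risk and benefit.

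**Working it through.** **1. The plan's own figure.** The Sample size calculation says "We aim to include 128 participants", for "d = 0.50 with a power (1-ß) of 80% and an alpha of 0.05". The normal approximation gives 2 × (1.96 + 0.84)² / 0.5² = 62.7, so 63 per arm. With the noncentral t (two-sided), power is 0.795 at 63 per arm and 0.801 at 64. The total of 128 reproduces, and n = 64 per arm is used below.

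**2. What the check tests and what it is used for.** The three-way term asks whether the difference in mean change between missing-data patterns itself differs by arm. It can be null while the harm comparison is biased in two ways.
- Those with missing data worsen equally in both arms, but more are missing in one arm. The three-way term is truly zero, yet the undercount is larger in the arm with more missing.
- A participant has no post-baseline HRSD-24. No change is observed, so the test reaches that person only through values imputed under the assumption in question.

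**3. Effect on the NNH.** Let p be the deterioration rate among the observed, m the missing share in an arm and q the rate among the missing. The arm's rate is (1 − m)p + mq. With equal p and q in both arms, the difference is (m₁ − m₀)(q − p), and NNH = 1/difference. The article gives none of these rates; p = 5% and all other inputs are assumptions.

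| Missing, GET.ON v OPD | q | Rates | Difference | NNH |
|---|---|---|---|---|
| 20% v 10% | 5% | 5% v 5% | 0 | none |
| 20% v 10% | 15% | 7% v 6% | 1 point | 100 |
| 20% v 10% | 25% | 9% v 7% | 2 points | 50 |
| 25% v 10% | 25% | 10% v 7% | 3 points | 33 |
| 20% v 10% | 100% | 24% v 14.5% | 9.5 points | about 11 |

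The row with q = 5% is what MI returns if it reproduces the observed rate. The last row is the extreme bound. With equal missing shares the difference in this set-up is zero whatever q is, although each arm's rate is still understated when q exceeds p. With more missing in OPD the sign reverses.

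**4. Does MI undercount?** A large-sample simulation assumed baseline and post-treatment SD 1, correlation 0.5, mean change −1 SD, and an RCI threshold of 1.96 × √2 × √(1 − 0.90) = 0.877 SD, taking the article's inter-rater reliability of 0.90. Imputation used random draws from the regression on baseline. True deterioration was about 3.0%. Entries are the rates after imputation.

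| Odds of dropout per SD of worsening | 10% missing | 20% | 30% |
|---|---|---|---|
| unrelated | 3.03% | 3.00% | 3.03% |
| × e^0.5 | 2.63% | 2.34% | 2.05% |
| × e^1 | 2.05% | 1.58% | 1.22% |

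At 20% missing and e^1, imputation assigns deterioration to 2.5% of the missing, against a true 9.8%. An imputation model that also used other scores from the same visit could narrow this gap.

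**5. Sensitivity of the check on its own terms.** With 20% of each arm in the incomplete pattern (12.8 v 51.2 per arm) and SD 1, the standard error of the interaction is √(2/12.8 + 2/51.2) = 0.442. Power is Φ(0.5/0.442 − 1.96) = 20% for an interaction of 0.5 SD and 62% for 1.0 SD.

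**The case against.** The strongest reply is that a condensed article commonly leaves a sensitivity analysis for a secondary binary outcome to an analysis plan that is not shown. That stands as far as the mere absence goes, and it also covers the unspecified imputation model. It does not cover the decision rule, which the article states: one test of mean severity change is to settle missing-data bias in the results generally.

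Other replies stand in part. Pattern-mixture analyses are introduced without being limited to one outcome, but only the severity interaction is described and tied to a conclusion. Deterioration is a cut of the same HRSD-24, so the check is related to it; it still does not test the count. The rule speaks of interactions in the plural, so lower-order terms might also be examined, but they too would concern mean change.

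The numbers are also modest against sampling error. At 9% v 7% the standard error of the difference is √(0.09 × 0.91/64 + 0.07 × 0.93/64) = 4.8 points, larger than the 1-3 point shifts in all but the extreme row.

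A reader might infer three stronger things that the document does not support:
- **That MI sets dropouts to an average value and so hides harm.** Proper MI draws with residual variation. In the simulation it recovers the true 3.0% when missingness is unrelated to worsening; single conditional-mean imputation is what puts almost none of the missing in the deteriorated class.
- **That the harm count has no protection.** The HRSD-24 is sought after treatment withdrawal, and stopping treatment is not the same as missing the interview. This does not close the gap, since participants may also leave the study and the Discussion expects missing values.
- **That the trial plans to declare no excess deterioration.** It plans to evaluate deterioration; its only no-harm hypothesis concerns attitudes towards seeking help.

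**Conclusion.** The point holds in a limited form. The check addresses mean change in depression severity, so its null result should not be taken to cover the number deteriorated, the NNH or the benefit-risk ratio. If people who worsen are more often missing, deterioration can be undercounted; if missingness also differs by arm, the NNH can be biased, in either direction, without the check showing it. An undercount concentrated in GET.ON could also keep the benefit-risk ratio from being calculated.

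That harm will be undercounted cannot be said. It depends on a dropout mechanism and on rates that the article does not give. On the assumed rates above, the shift is 1-3 percentage points in the moderate cases and 9.5 points at the extreme bound. The point does not touch the sample size or the choice of MI for the main estimate.

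**What to change.** 1. Keep MI for the main estimate.
2. Reword the conclusion drawn from the interaction test so that it concerns mean severity change only, and say that it does not extend to deterioration, the NNH or the benefit-risk ratio.
3. For deterioration and the NNH, add a sensitivity analysis that departs from the MI assumption: either a delta adjustment that worsens the imputed HRSD-24 scores, or a tipping-point grid in which the deterioration rate among the missing varies separately by arm. Use all missing counted as deteriorated in both arms as the extreme bound.
4. Report the NNH with the range that results, next to the number missing in each arm.

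The cost is a few sentences in the analysis plan and a few extra runs on data already being collected. The price is a wider and slightly less favourable harm estimate.

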This study will also have some limitations. First, as in most longitudinal studies we will need to deal with the problem of missing values. Although the planned adjustment for missing data (Multiple Imputation) is a highly recommended method to handle missing data [62], we will nevertheless additionally conduct pattern-mixture analyses [63] to minimise a possible risk for bias. Second, ideally the risk for negative effects when providing an Internet-based guided self-help intervention to patients with MDD needs to be compared with the risk for negative effects in face-to-face psychotherapy. However, a systematic evaluation of potentially negative effects of treatment has seldom been conducted for face-to-face psychotherapeutic interventions for Major Depression. Therefore, drawing conclusions on the differential risk of this guided self-help treatment compared to traditional psychotherapeutic treatment will not be possible. Third, the comparison condition does not control for unspecific effects through human support. Finally, the study sample will be too small to test for potential moderating effects. Thus, which patients are likely to profit from this type of treatment delivery or which patients are especially likely to experience negative effects will remain unclear.

There will also be several strengths of this study, including the strong methodology of a randomised controlled design with an active control condition, outcome assessment with validated assessments by independent raters blind to treatment condition, a sample defined by a standard diagnostic measure, an appropriate statistical analyses plan and handling of missing data with state of the art methods. Given these strengths, the results of the study should further enhance the evidence-base for Internet-based guided self-help interventions for Major Depression. Moreover, a systematic evaluation of potentially negative effects of an Internet-based treatment as it is conducted in the present study has to the best of our knowledge not been conducted before. This study will therefore provide valuable information to the field as the basis for a wide dissemination of such concepts.

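### A non-significant missing-pattern interaction is taken to show that missing data caused no bias, but the test has low power and observes no change in participants with only a baseline score

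*Protocol article*

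**What the plan says.** The Statistical analyses section plans intention-to-treat mixed models with multiple imputation for missing values. It then adds a further analysis: "to assess systematic effects of non-ignorable missing data, pattern mixture analyses for multi-level longitudinal approaches". Each participant's missing-data pattern is to be coded and "included in a three-way interaction (missing pattern × condition × change in depression severity) in the main outcome analyses". The rule for reading the result follows: "If no significant interactions between missing-data pattern and treatment outcome are found, we will conclude that no missing data bias occurred in the results".

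The limitations paragraph of the Discussion returns to the topic, saying that "we will nevertheless additionally conduct pattern-mixture analyses" so as to reduce a possible risk of bias. It neither repeats nor withdraws the rule. The same paragraph concedes that the sample is too small to examine moderation.

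On size, the Sample size calculation section says "We aim to include 128 participants", enough to "detect a between-group effect size (ES) of d = 0.50 with a power (1-ß) of 80" per cent. No dropout rate is given. The Design section and Table 2 place HRSD-24 at baseline (T1), 6 weeks (T2) and 12 weeks (T3), so there are two post-baseline measurements.

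**The concern.** The rule turns a failure to reject into a positive finding. That would be unsound at any sample size, and two features of this trial make it worse.

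First, the test asks whether the treatment effect differs between missing-data patterns. It is an interaction test that depends on a small incomplete group, in a trial sized only for the main effect.

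Second, the stated purpose is to examine non-ignorable missingness. Someone who has a baseline HRSD-24 and nothing afterwards shows no change, so observed data cannot say how the treatment effect in that group compares with the rest.

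At stake is the claim attached to the primary HRSD-24 result. A trial with informative loss could be reported as shown to be free of missing-data bias on the strength of a check that could hardly have found it.

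**Working it through.** **1. The plan's own figure.** Inputs from the Sample size calculation section: d = 0.50, 80% power, alpha 0.05, total 128. Sidedness and allocation ratio are not stated; I take two-sided and 64 per arm. The noncentral t distribution gives 80.1% power at 64 per arm and 79.5% at 63, so 128 is reproduced. One-sided testing would need only 100. The trial is therefore sized for the main effect alone.

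**2. Power of the interaction test.** Take the contrast on T1-to-T2 change, in units of the cross-sectional SD, with ρ the baseline-to-T2 correlation:

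- SD of change = √(2(1 − ρ)), which is 1 at ρ = 0.5.
- SE = SD of change × √(4/n_complete + 4/n_incomplete), counting only participants observed at T2.
- Power = Φ(Δ/SE − 1.96) + Φ(−Δ/SE − 1.96).

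I set Δ = 0.50 SD: the full planned effect in one pattern and none in the other. Dropout, the share of incomplete cases still seen at T2, and ρ are assumptions.

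Worked case: with 20% dropout, all seen at T2, n_incomplete = 25.6 and n_complete = 102.4. Then SE = √(4/102.4 + 4/25.6) = 0.442, Δ/SE = 1.13, and power is 20.5%.

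Power at ρ = 0.5, Δ = 0.50 SD:

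| Dropout | All incomplete cases seen at T2 | Half seen | A quarter seen |
|---|---|---|---|
| 10% | 13.6% | 9.4% | 7.3% |
| 20% | 20.5% | 13.5% | 9.4% |
| 30% | 25.4% | 16.9% | 11.4% |
| 40% | 28.3% | 19.5% | 13.1% |

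Over ρ = 0.3 to 0.7 the range is about 7 to 43%. At ρ = 0.5 the difference detectable with 80% power is 1.0 to 3.2 SD, against a planned main effect of 0.50. In the worked case SE = √(25/N), so 80% power needs N = 25 × (2.80/0.50)², about 785 participants.

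**3. Participants with a baseline score only.** Suppose everyone lost before T2 stays lost and those in GET.ON gain nothing, while everyone else has the planned effect. The true intention-to-treat effect is 0.50 × (1 − dropout × share lost before T2). Imputation under MAR gives the lost participants the same effect as the observed ones, so its estimate stays near 0.50. Simulation of 1,500 trials per scenario:

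| Dropout | Share lost before T2 | True effect | Mean estimate after MAR imputation | Interaction significant, observed data | Interaction significant, after MAR imputation without pattern |
|---|---|---|---|---|---|
| 20% | 50% | 0.45 | 0.50 | 4.5% | 0.1% |
| 30% | 50% | 0.425 | 0.50 | 5.7% | 0.3% |
| 30% | 75% | 0.39 | 0.50 | 5.1% | 0.0% |

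On observed data the test rejects at about its alpha level, because nothing observed distinguishes these participants. After imputation without the pattern it rejects even less often, because the filled-in values carry no interaction. In these scenarios the rule reports no bias in about 95 to 100% of trials.

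**The case against.** Several points on the other side hold.

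- **Power is not negligible everywhere.** A reader might infer that the test has almost no power. That goes too far: for a 1.0 SD difference with 40% dropout, all seen at T2, power is about 79% at ρ = 0.5 and 95% at ρ = 0.7. The article supports low power for differences on the scale of the planned effect, and only under assumed dropout.
- **Missing T2 is not the same as having no follow-up.** A reader might infer that nothing is known about anyone absent at T2. Someone who returns at T3 informs the T1-to-T3 change. The gap concerns those with a baseline score alone.
- **Near-zero detection is conditional.** The article puts the interaction into the main outcome analyses but does not say whether these use observed or imputed data. A pattern-mixture model can be fitted to observed data, where detection is about 5%.
- **The data may be better than the scenarios.** The Assessments section separates telephone HRSD-24 ratings from online self-report, and Table 2 lists PHQ-9 at T2 and T3. A missing HRSD-24 therefore need not leave the imputation without post-baseline depression data. People who withdraw from treatment are also asked for at least the primary outcome (Assessment of eligibility and randomisation).
- **The Discussion is more cautious.** It speaks of reducing a risk of bias and does not repeat the fault.

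These points limit the size of the problem. None makes a non-significant result into evidence that bias is absent. Nor is this detail left to an analysis plan: the rule is stated outright and nothing in the article qualifies it.

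**Conclusion.** The concern holds for the decision rule and should be fixed. For a 0.50 SD difference between patterns, power is about 7 to 28% at ρ = 0.5 and at most about 43% at ρ = 0.7, over assumed dropout of 10 to 40%. For non-ignorable loss with only a baseline score, detection is about 5% on observed data and about 0% after MAR imputation that omits the pattern.

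A reader might go on to infer that the primary result will be inflated. The article does not support that. The direction follows only if GET.ON dropouts do worse than predicted, and 0.50 against 0.39 to 0.45 is illustrative. Multiple imputation and the pattern-mixture analysis are reasonable in themselves. The primary estimate stands whatever the interaction shows; what the rule distorts is the claim about its robustness. That is why this is a should-fix and not a must-fix.

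**What to change.** 1. Delete the sentence that concludes no bias occurred.
2. Keep the pattern-mixture analysis. Report pattern-specific and pattern-averaged treatment effects with confidence intervals, and state what is assumed for the baseline-only pattern, whose effect cannot be estimated from observed data.
3. Add a sensitivity analysis of the T2 HRSD-24 effect that departs from MAR. Delta-adjusted (tipping-point) or reference-based multiple imputation would both serve; other choices are possible. Judge robustness by how large a departure is needed to change the conclusion.

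The cost is revised wording, a few extra analysis runs and a more cautious statement about missing data. No new participants or measurements are needed.

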#### Assessment of eligibility and randomisation

People who apply for study participation will receive an information letter with detailed information about the study procedures. Full written informed consent will be obtained from all participants. They will be informed that they can withdraw from the intervention and/or study at any time without any negative consequences. Nevertheless, we will ask those who withdraw from the trial treatment to attend all the remaining research appointments or at least provide minimal data (primary outcome measure). Applicants who continue to participate in the study will be asked to complete online screening questionnaires to assess the severity of their depressive symptoms (CES-D >16), whether they are currently receiving any kind of treatment for any mental health disease and whether they have a high suicidal risk (BDI Item 9 > 1). Subjects screened positive and are willing to give informed consent will be scheduled for a structured clinical interview (SCID) conducted via the telephone [27]. SCIDs will be conducted by trained clinicians. Participants meeting all of the inclusion and none of the exclusion criteria, who have completed the baseline assessment, and returned the informed consent form will enter the study and will be randomly allocated to study conditions. Randomisation will take place at an individual level. The allocation will be performed by an independent researcher not otherwise involved in the study using an automated computer-based random integer generator (randlist). The allocation will be concealed in advance from participants, researchers involved in recruitment, and therapists.

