##### Response and remission

Participants will be coded as responders when they demonstrate a reliable change according to the widely used reliable change index (RCI) [58]. Participants with an RCI of 1.96 or above on the primary outcome measure HRSD_24_ will be considered responders. Remission is defined a priori as a non-pathological score of ≤10 on the HRSD_24_.

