		**Time of measurement**		
**Instrument**	**Aim**	**T1 ****(****Baseline****)**	**T2 ****(****6 weeks****)**	**T3 ****(****12 weeks****)**
**SCID**	Diagnostic interview	x		
**HRSD**_ **24** _	Hamilton Rating Scale for Depression	x	x	x
**QIDS**-**C**_ **16** _	Quick Inventory for Depressive Symptomatology	x	x	x
**PHQ**-**9**	Depressive symptomatology	x	x	x
**WHO**-**5**	Wellbeing	x	x	x
**SF**-**12**	Quality of life	x	x	x
**HADS**-**A**	Anxiety symptoms	x	x	x
**SPSI**-**R**	Problem-solving skills	x	x	x
**BADS**-**SF**	Behavioural activation	x	x	x
**CEQ**	Patient expectancy/treatment credibility	x		
**ATSPPH**-**SF**	Attitudes toward seeking psychological help	x	x	
**BFI**	Big Five Inventory	x		
**INEP**	Inventory of negative effects in psychotherapy		x	x
**CSQ**-**8**	Clients’ satisfaction with the online training		x	
**AUDIT**	Alcohol use disorder identification test	x		
**Other questions**	Socio-demographics	x		

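### Response and remission are compared by unadjusted χ2 tests although baseline HRSD-24 is available for everyone randomised: valid, but it gives up some precision in two secondary endpoints and their NNTs

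*Protocol article*

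**What the plan says.** All references are to the protocol article.

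- **Test.** Statistical analyses: "Response and remission rates will be compared across groups with the help of contingency tables and χ2 tests". No covariate is named.
- **NNT.** Same section: "We will also calculate the number needed-to-be-treated (NNT) with GET.ON Mood Enhancer to achieve one response and remission, respectively, compared to the control group". The estimator is not spelled out. Crude rates are the natural reading, since the sentence follows directly on the χ2 tests. The response NNT is also the denominator of the benefit-risk ratio, which is calculated only if the groups differ significantly in deterioration risk.
- **Endpoints.** Response and remission: "Participants with an RCI of 1.96 or above on the primary outcome measure HRSD_24_ will be considered responders", and "Remission is defined a priori as a non-pathological score of ≤10 on the HRSD_24". One is a change from baseline, the other an absolute score. The Primary and secondary outcomes section lists both under the secondary analyses.
- **Baseline.** Table 2 schedules the "Hamilton Rating Scale for Depression" at T1, T2 and T3. Under Assessment of eligibility and randomisation, it is those "who have completed the baseline assessment, and returned the informed consent form will enter the study and will be randomly allocated to study conditions", so the T1 score exists for everyone randomised.
- **Allocation.** "Randomisation will take place at an individual level". The article describes no balancing on severity.
- **Other models in the plan.** Continuous outcomes go into mixed models. Logistic regression is named for binary outcomes among the other negative effects. All analyses are to be run in SPSS 20.

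**The concern.** Baseline HRSD-24 should predict both endpoints. A participant who starts with a higher score has further to fall to reach 10 or less, so remission is less likely. The same participant tends to show a larger fall through regression to the mean, so a reliable change is more likely. No HRSD-24 range is required for entry (the criteria are an MDD diagnosis and a CES-D screen), so baseline severity may vary considerably.

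A crude comparison leaves this predictable variation in the error. Two things follow, and they are the same loss seen from two sides. Over repeated randomisations, the risk differences are less precise than the collected data allow. In the allocation that actually occurs, a chance difference in baseline severity passes into the crude risk differences and the NNTs. Because the dependence on baseline has opposite signs, the response and remission NNTs are pushed apart or together for a reason unrelated to treatment.

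**Working it through.** **1. The plan's own figure.** For d = 0.50, two-sided alpha 0.05 and 80% power, n per arm = 2 × (1.960 + 0.842)² / 0.50² = 62.8, so 63 per arm and 126 in total. The noncentral t with 64 per arm gives power 0.801. The stated 128 is reproduced. It is set for the continuous outcome and does not depend on this point.

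**2. Inputs for the binary endpoints.** From the protocol: N = 128 (64 per arm assumed), d = 0.50, remission cut-off 10, RCI criterion 1.96. Assumed, because the article does not give them: baseline HRSD-24 mean 24, SD 7; control post-treatment mean 18, SD 8; correlation ρ between baseline and post-treatment scores of 0.3, 0.5 or 0.7; no dropout. The stated inter-rater reliability of 0.90 is used in the RCI as an assumption, so response is a fall of at least 1.96 × 7 × √(2 × 0.10) = 6.1 points.

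Check on the rates: d = 0.50 puts the GET.ON mean at 18 − 0.5 × 8 = 14. Remission is then Φ((10 − 18)/8) = 15.9% in control and Φ((10 − 14)/8) = 30.9% with GET.ON, a difference of 15 points (NNT 6.7).

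**3. Simulation, 4,000 runs per row.** The crude risk difference (RD) is set against the RD standardised from a logistic model with baseline. Power is Φ(RD/SD − 1.96), where SD is the sampling SD of the RD. The slope is the change in the crude RD per baseline SD by which GET.ON starts more severe.

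| Endpoint | ρ | Mean RD | SD crude → adjusted | Power crude → adjusted | Slope, crude |
|---|---|---|---|---|---|
| Remission | 0.3 | 0.149 | 0.0724 → 0.0706 | 0.54 → 0.56 | −0.094 |
| Remission | 0.5 | 0.148 | 0.0744 → 0.0696 | 0.51 → 0.57 | −0.152 |
| Remission | 0.7 | 0.151 | 0.0726 → 0.0619 | 0.55 → 0.68 | −0.201 |
| Response | 0.3 | 0.174 | 0.0848 → 0.0772 | 0.54 → 0.62 | +0.202 |
| Response | 0.5 | 0.203 | 0.0850 → 0.0814 | 0.67 → 0.71 | +0.147 |
| Response | 0.7 | 0.255 | 0.0824 → 0.0817 | 0.87 → 0.88 | +0.082 |

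Crude and adjusted mean RDs agree to within 0.001, so the quantity estimated does not change. After adjustment the slope is at most 0.011 in absolute value. Under no effect, the χ2 test rejects in 4.5% to 5.0% of runs.

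A second set of assumptions (standardised scores; control remission 20% or 35%; control response 28% or 39% at ρ = 0.5) gives gains of about 2 to 15 points for remission and 3 to 11 for response. Over both sets the ranges are about 2 to 15 and about 0.5 to 11.

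**4. Chance imbalance.** The SE of the baseline mean difference is √(2/64) = 0.177 SD. A one-SE imbalance shifts the crude RD by slope × 0.177:

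- Remission: 0.094 × 0.177 = 0.017 (ρ = 0.3) to 0.201 × 0.177 = 0.036 (ρ = 0.7). The NNT runs from 6.0 to 7.6 and from 5.4 to 8.7 respectively.
- Response: 0.202 × 0.177 = 0.036 (ρ = 0.3) to 0.082 × 0.177 = 0.015 (ρ = 0.7). The NNT runs from 4.8 to 7.2 and from 3.7 to 4.2 respectively.

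Example at ρ = 0.5, with GET.ON one SE more severe at baseline: the remission RD falls from 14.8 to 12.1 points (NNT 6.8 to 8.3), while the response RD rises from 20.3 to 22.9 points (NNT 4.9 to 4.4).

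**5. The two effects are one.** For remission at ρ = 0.5, take the imbalance component out of the crude SD, using the simulated imbalance SD of 0.174: √(0.0744² − (0.152 × 0.174)²) = 0.0695, which matches the adjusted SD of 0.0696.

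**The case against.** The case for leaving the plan alone is substantial. The χ2 test of two randomised proportions is valid and needs no model. The endpoints are secondary and described as explored. The primary analysis already works with change from baseline on the continuous score. Every figure above rests on a correlation, rates and a reliability that the article does not supply. For response at ρ = 0.7 the gain is almost nil, because the RCI already subtracts baseline. The imbalance shift is modest against sampling error: 2.7 points for remission at ρ = 0.5 is about 0.36 of the crude SE of 7.4 points, and the crude interval already covers it (step 5). All of this stands, and it limits the point to an improvement in efficiency.

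It does not remove the point. The unadjusted test is a stated choice, not a detail left to an unseen document. The covariate is already collected, and adjustment reduced the SD in every scenario.

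Some stronger inferences are tempting but not supported:

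- *That the χ2 test or the NNTs are biased.* They are not, over randomisations. Imbalance matters only for the realised allocation.
- *That the strongest predictor in the trial is thrown away.* Nothing in the article ranks predictors, and baseline is used for the continuous outcomes.
- *That large shifts are to be expected.* A gap above 0.3 SD, worth about 5 to 6 points at ρ = 0.5 under the second set of assumptions, has only about a 9% chance: 2 × (1 − Φ(0.3/0.177)).
- *That differing response and remission NNTs indicate imbalance.* They measure different things and need not agree.
- *That the article's silence on stratification or on the NNT formula is a defect.* A condensed article may leave both to the full protocol or analysis plan. They enter here only as assumptions.
- *That power gains read from likelihood-ratio tests (up to about 16 to 17 points for remission and 13 for response) can be taken at face value.* That test rejected in 5.0% to 6.0% of null runs on the HRSD scale, so part of such a gain may be spurious.

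**Conclusion.** The point holds as a small-cost improvement to a stated method. The planned comparison is valid but less precise than the data allow. The loss is about 2 to 15 power points for remission and about 0.5 to 11 for response, and a one-SE baseline imbalance moves the crude risk differences by about 1.5 to 4 points in opposite directions. This carries into the NNTs and, if it is calculated, the benefit-risk ratio. These sizes depend on assumed correlations of 0.3 to 0.7, 1:1 allocation without balancing on severity, no dropout, an RCI reliability of 0.90, and NNTs taken from crude rates. Type I error, the primary conclusion and the sample size are not in question.

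**What to change.** In Statistical analyses, before any unblinded analysis:

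- Make logistic regression on condition and continuous T1 HRSD-24 the main comparison for response and for remission.
- Obtain the risk difference and NNT, each with a 95% CI, by marginal standardisation over all randomised participants, so that the NNT remains a population-level figure. Pool over the multiply imputed data sets already planned.
- Base inference on the standardised risk difference and its interval, not on the likelihood-ratio test, which may be slightly liberal at this N.
- Keep the contingency tables and χ2 tests as supporting description.

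No new data or participants are needed, and logistic regression is already in the plan for other outcomes. The costs are an assumption that the log-odds are linear in baseline HRSD-24, and extra programming: standardised risk differences with intervals pooled over imputations go beyond standard SPSS 20 output, so the single-software statement may need an exception.
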